### Primary qualitative data collection

The qualitative data collection methods include semi-structured interviews and FGDs; structured observations of PLH-Teens group sessions conducted by facilitators; structured observations of facilitator supervision sessions conducted by coaches; analysis of policies, progress reports, and other documents anonymized and voluntarily provided by Pact Tanzania and CWBSA; and field notes taken by researchers during community of practice meetings with stakeholders. Qualitative data collection tools have been developed based on the EPIS framework and Proctor’s taxonomy. The interview, FGD, and observation guides cover relevant parts of the implementation process experienced by various participants (see Open Science Framework). For example, questions for facilitators focus on the implementation process since they are most familiar with implementation while questions for Pact managers emphasize exploration and sustainment.

#### Interviews and FGDs

Interviews will be conducted with coaches (*N* = 16), facilitators (*N* = 16), LIP staff (*N* = 8), school principals (*N* = 8), and CWBSA staff (*N* = 3). FGDs will be held with coaches (*N* = 32, 8/FGD), facilitators (*N* = 80, 10/FGD), parents/caregivers (*N* = 80, 10/FGD), and adolescents (*N* = 80, 10/FGD). All interviews (approximately 60–90 min) and FGDs (approximately 90–120 min) will be conducted in Kiswahili based on semi-structured guides (see Open Science Framework). The guides provide an outline of key topics and questions for the interviewers to ask study participants as well as leave room to delve into pertinent issues that emerge during interviews and FGDs. All interviews and FGDs will be audio-recorded with the permission of the participants. Where a participant declines, permission will be sought for field notes to be taken instead. Interview and FGD participants will be provided with lunch and transportation to and from the meeting venues (approximately $10–15 USD). In cases where face-to-face interviews and FGDs are not possible, interviews will be conducted remotely via telephone. While the importance of confidentiality will be emphasized during FGDs, participants will be informed about how limited researchers are in their ability to enforce post-discussion adherence to confidentiality commitments made by FGD participants.

#### Session observations

To better understand the implementation fidelity of PLH-Teens, researchers will conduct observations of program delivery and supervision sessions. Program participants and facilitators will be observed during program sessions (*N* = 5 sessions; 150 participants) and facilitators and coaches will be observed during supervision sessions (*N* = 5 sessions; 50 participants). The exact locations of the five program observations will be selected by the implementation team to take the variation and contextual factors of each district into consideration. A random selection of five coaching observations will be conducted in consultation with Pact Tanzania. Observations of program sessions and supervision sessions will follow structured observation guides (see Open Science Framework).

#### Document analysis

The researchers will conduct content analyses of Pact Tanzania and CWBSA reports to identify implementation barriers and supports as well as to determine how PLH-Teens fits within the larger Kizazi Kipya Project. Formal requests will be sent to partner organizations seeking permission to review and analyze relevant documents, with sensitive information redacted before the documents are shared and analyzed.

#### Community of practice meetings

Following program delivery, stakeholder engagement meetings will be held with government and non-government stakeholders involved in the implementation of PLH-Teens (*N* = 2 sessions; 50 participants). In these meetings, stakeholders will be asked to provide an overview of their experiences, including challenges implementing the program and possible solutions to the challenges identified. These participatory community of practice meetings will be held in Dar es Salaam during which researchers will take field notes.

### Secondary quantitative data collection

The study will analyze the following anonymized secondary process and outcome data from Pact Tanzania and CWBSA: pre-post surveys completed by parent/caregivers (*N* = 50,000); pre-post surveys completed by adolescents (*N* = 50,000); parent/caregiver and adolescent program attendance registers (*N* = 100,000 participants); facilitator demographic questionnaires (*N* = 444); coach demographic questionnaires (*N* = 70); coach assessments of facilitators (*N* = 444); CWBSA assessments of coaches (*N* = 70); LIP organizational surveys (*N* = 5); and implementation cost surveys (*N* = 300).

#### Family outcome and demographic measures

Pact Tanzania was provided with a set of process and outcome tools by CWBSA as part of the monitoring and evaluation technical support they provide to all implementing partners delivering PLH programs. CWBSA recommends and provides these tools because they are open-access and have been psychometrically tested in previous studies. Due to the large number of beneficiaries Pact Tanzania is reaching and their limited capacity to collect evaluation data, they are using abbreviated versions of the tools provided by CWBSA. An overview of these tools and their items is summarized in Additional file 8.

#### Implementation process measures

Pact Tanzania, LIPs, and CWBSA will collect data about parents/caregivers and adolescents (e.g., attendance), facilitators (e.g., demographic characteristics, fidelity), and coaches (e.g., demographic characteristics, fidelity) (see OSF page). The data will be used to understand the quality of program implementation, the factors that predict implementation outcomes, how implementation varies from context to context, and how implementation is associated with intervention outcomes. In particular, information about participant attendance, staff demographics, facilitator competent adherence, coach competent adherence, and organizational characteristics will be collected using a variety of measures (see Additional file 8). For example, data on facilitator competent adherence will be collected by Pact coaches using the PLH-Facilitator Assessment Tool for Teens (PLH-FAT-T)—an observational assessment tool administered by coaches based on live observations or video recordings of group sessions. Facilitator competent adherence is the skill with which a facilitator delivers intervention components and the strictness with which they follow the activities outlined in the program manual [50, 51]. All of the implementation data collected will be linked to parent/caregiver and adolescent outcomes through the use of unique identifiers supplied by LIPs, which will make it possible to link data from multiple sources. The data will be anonymized by the LIPs before it is shared with researchers.

#### Cost measures

Information about the time and resource costs of program set-up and implementation will be collected by Pact from facilitators, coaches, and LIP coordinators to determine how much program delivery costs at scale. Costing information will be collected using surveys which ask participants for retrospective estimates of the amount of time used or money expended on a program activity (see OSF page). The surveys were created based on resources provided by The Abdul Latif Jameel Poverty Action Lab. The collection of cost information will also include a review of program budgets, spending, and other data obtained from Pact Tanzania about the resources required to set-up and deliver the program.

### Data analysis

#### Qualitative analyses

Qualitative data will be transcribed verbatim and translated into English. Analysis will be conducted using NVIVO 12 qualitative analysis software. Multiple researchers will review a sample of the interview and FGD transcripts to generate a coding framework based on the research questions. Following the creation of the coding scheme, the data will be double coded to establish reliability among the researchers. Thereafter, data-driven coding will be used to identify concepts, relationships, and broad themes (thematic analysis). The findings will then be discussed by the research team to identify overarching themes and to select data segments that represent the key themes and divergent viewpoints. Where appropriate, COREQ standards will be used when reporting qualitative data [52].

#### Quantitative analyses

Quantitative data will be cleaned using Stata and analyzed in Stata and R using methods such as correlation and regression analyses, as well as structural equation models. The frequencies and distribution of each variable will be examined to check for any implausible values as well as to select the appropriate analysis method (e.g., a suitable regression link function). When there are more than two items in a given scale, coefficients such as Cronbach Alphas or Omegas will be used to assess the item-level reliability of the measures. Where possible, mixed effect models will be utilized to account for nesting within parenting groups [53]. Missing data will be addressed appropriately by considering the complete case observations as well as using full information maximum likelihood or multiple imputation, as appropriate [54, 55]. Where relevant, TREND guidelines will be used when reporting quantitative results [56].

#### Research question 1

The level of implementation of PLH-Teens delivery will be determined by analyzing data from family attendance registers; facilitator assessments; coach assessments; structured observations of group sessions; interviews held with facilitators, coaches, and LIP staff; and FGDs held with adolescents, parents/caregivers, facilitators, and coaches. Attendance rates and attendance trends among parents/caregivers and adolescents, as well as variations in attendance, and program completion rates will be calculated based on the attendance registers to determine the extent of participation in PLH-Teens. The level of competent adherence with which facilitators deliver the program will be determined using the results from the Facilitator Assessment Tool assessments completed by coaches. To examine the reliability and validity of the Facilitator Assessment Tool, a psychometric evaluation consisting of content validity (stakeholder perspectives from interviews and focus groups with facilitators, coaches, and CWBSA staff), intra-rater reliability (percentage agreements and intra-class correlations), inter-rater reliability (percentage agreements and intra-class correlations), internal consistency (Cronbach Alphas), construct validity (exploratory factor analyses), and predictive validity analyses will be performed. Similarly, the level of competent adherence with which coaches deliver facilitator supervision will be determined using the results from the Coach Assessment Tool assessments completed by CWBSA staff. Interviews, FGDs, and session observations will be used to expand upon and contextualize the findings regarding the demographic, attendance, facilitator competent adherence, and coach competent adherence data.

#### Research question 2

Factors associated with the quality of implementation will be examined using the socio-demographic data from the Facilitator and Coach Profile Forms; LIP organizational characteristics surveys; interviews; FGDs; and structured observations of group sessions. Correlation and regression analyses will be used to examine the relationship between facilitator and coach competent adherence and their associations with family, facilitator, coach, and organizational characteristics. Interviews, FGDs, and session observations will be used to expand upon and contextualize the findings.

#### Research question 3

A variety of data sources will be used to examine how implementation is associated with changes in VAC and family well-being. In particular, correlation and regression analyses will be used to look at whether pre-post changes in family outcomes are associated with family attendance, facilitator and coach competent adherence, and facilitator and coach characteristics, as well as LIP characteristics. Interviews, FGDs, and session observations will be used to expand upon and contextualize the findings.

#### Research question 4

Participant and implementing staff perspectives on the acceptability, appropriateness, feasibility, benefits, and challenges of delivering PLH-Teens in their communities will be examined by analyzing the interviews, FGDs, and session observations with school principals, facilitators, coaches, LIP staff, CWBSA staff, adolescents, and parents/caregivers.

#### Research question 5

Changes in VAC and participant well-being will be analyzed based on data gathered from parent/caregiver pre-post questionnaires, adolescent pre-post questionnaires, interviews, and FGDs. Multi-level models will be used to examine differences in pre- to post-intervention family-level outcomes and to compare differences in outcomes reported by both adolescents and parents/caregivers. Variation in the pre-post changes will be examined by participant baseline characteristics, and, if possible, by parenting group and LIP. The analyses will be similar to treatment-on-the-treated analyses since all participants included in the monitoring data would have engaged with the program to some extent. The levels of change reported by participants will be compared to the levels of change reported by the treatment and control groups in the randomized trial of the program in South Africa. Where possible, the reliability of the family survey items will also be examined using coefficients such as Cronbach Alphas or Omegas.

The findings from the interviews and FGDs  will also be analyzed to explore participant perspectives on the impacts of the program on them and their families. The interviews and FGDs will also reveal what impact implementing volunteers and staff assess the program had and will have on themselves, participants, schools, and communities.

#### Research question 6

The cost of delivering PLH-Teens at scale will be calculated using retrospective cost estimates provided by facilitators, coaches, and LIP coordinators and costing data provided by Pact Tanzania. Average costs will also be calculated and summarized for each program component (e.g., facilitator training, group sessions, supervision), family (parent/caregiver-adolescent dyad), district, and facilitator type (community volunteer or teacher).

A summary of the data that will be analyzed to answer each of the FAIR study’s six research questions is shown in Table 4.

**Table 4 Tab4:** Evaluation matrix

Evaluation question	Data source
RQ1: What is the level of program implementation of PLH-Teens at scale in Tanzania in terms of quality of delivery and implementation fidelity?	1) Parenting for Lifelong Health-Facilitator Assessment Tool (PLH-FAT)—measures facilitator competence and adherence 2) Direct observation of group sessions using the structured observation guide 3) Semi-structured interviews held with facilitators, coordinators, coaches, and LIP staff 4) Focus group discussions (FGDs) held with adolescents, parents/caregivers, facilitators, and coaches
RQ2: What factors are associated with the quality of delivery and implementation fidelity of PLH-Teens?	1) PLH-FAT 2) Interviews 3) FGDs 4) Community of practice reflective meetings among LIPs, Pact, CWBSA and researchers 5) Facilitator Profile Form examining facilitator demographics including education level, experience, and professional background 6) Coach Profile Form examining coach demographics including education, experience, and professional background 7) LIP Organizational Characteristics Form 8) Direct observation of group sessions using the structured observation guide
RQ3: How are implementation quality and fidelity associated with intervention outcomes?	1) PLH-FAT 2) Interviews 3) FGDs 4) Community of practice reflective meetings 5) Facilitator Profile Form 6) Coach Profile Form 7) LIP Organizational Characteristics Form 8) Parent/caregiver- and adolescent-report on pre-post questionnaires 9) Parent/caregiver and adolescent program attendance data 10) Direct observation of group sessions using the structured observation guide
RQ4: What are participant and implementing staff perspectives on the acceptability, appropriateness, feasibility, benefits, and challenges of delivering PLH-Teens in their schools and communities?	1) Interviews with school principals, facilitators, coordinators, coaches, and LIP staff 2) FGDs with adolescents, parents/caregivers, facilitators, and coaches 3) Direct observation of group sessions using the structured observation guide
RQ5: What is the impact of PLH-Teens on VAC and participant well-being?	1) Parent/caregiver- and adolescent-report on pre-post questionnaires 2) Individual interviews with school principals, facilitators, coordinators, coaches, and LIP staff 3) FGDs with adolescents, parents/caregivers, facilitators, and coaches
RQ6: How much does it cost to deliver PLH-Teens at scale?	1) Facilitator cost surveys 2) Facilitator profile surveys 3) Coach cost surveys 4) LIP cost surveys

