### PLH-Teens in Tanzania

Encouraging results from the cluster RCT [37] have contributed to the rapid dissemination of PLH-Teens in 16 countries to approximately 300,000 beneficiaries. Among these is the large-scale implementation of PLH-Teens in Tanzania that started in 2017 as part of the Kizazi Kipya (or “New Generation”) Project by Pact Tanzania. Kizazi Kipya is a USAID-PEPFAR-funded project aiming to enable more Tanzanian orphans and vulnerable children (OVC)—children, adolescents, and young people orphaned and made vulnerable by HIV and other adversities—to use age-appropriate HIV- and AIDS-related and other services for improved care, health, nutrition, education, protection, livelihoods, and psychosocial well-being. Through Kizazi Kipya, Pact Tanzania implements the DREAMS Initiative (Determined, Resilient, Empowered, AIDS-free, Mentored, and Safe) which aims to reduce HIV infection among adolescent girls and young women in HIV priority areas. As part of DREAMS, Pact is implementing the locally adapted and HIV-enhanced version of PLH-Teens, known as the Furaha Caring Families Program for Parents and Teens (Furaha Teens), for adolescent girls aged 9–14 and their parents/caregivers.

In 2020–2021, Pact is scaling-up PLH-Teens with 444 trained facilitators and 70 coaches to reach an additional 100,000 beneficiaries (approximately *N* = 50,000 adolescents and *N* = 50,000 parents/caregivers). The 2020–2021 delivery of PLH-Teens in Tanzania offers an unprecedented opportunity to examine the intervention and implementation outcomes when delivered at scale. As a result, this study—the Furaha Adolescent Implementation Research or FAIR study—will provide vital information on how to establish, implement, improve, and sustain high-quality delivery of PLH-Teens. The findings will also be of value to other parenting programs aiming to prevent VAC at scale.

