### Study participants

The study will collect primary data from 48 program coaches, 96 program facilitators, 58 Pact Tanzania and LIP staff, eight school principals, three CWBSA staff, 155 parents/caregivers, and 155 adolescents. The study will also collect anonymized secondary data from approximately 50,000 parent-child dyads (*N* = 100,000), 444 program facilitators, 70 program coaches, and five LIPs. The inclusion criteria used to select study participants for primary and secondary data collection are outlined in Tables 2 and 3.

**Table 2 Tab2:** Inclusion criteria for primary data study participants

Study participant group	Primary data inclusion criteria
Program Coaches (*N* = 70)	• Attended the Furaha Teens coach training workshop; and • Provided coaching to facilitators during the implementation of Furaha Teens.
Program Facilitators (*N* = 444)	• Teachers or community volunteers; • Attended the Furaha Teens facilitator training workshop; and • Implemented the Furaha Teens program.
Pact Tanzania and LIP Staff (*N* = 58)	• Staff member working for either Pact Tanzania or one of the LIPs delivering Furaha Teens.
School Principals (*N* = 8)	• Principal in a school where Furaha Teens was delivered.
CWBSA Staff (*N* = 3)	• Staff member working for CWBSA involved in the implementation or research associated with the FAIR Study.
Parents/caregivers (*N =* 155)	• Aged 18 or older; • Primary caregiver responsible for the care of an adolescent between the ages of 9 and 14 who attended the Furaha Teens program; and • Attended in the Furaha Teens program.
Adolescents (*N =* 155)	• Aged 9 to 14; • Consent provided by primary caregiver responsible for the adolescent’s well-being; • Assent provided by the adolescent; • Primary caregiver responsible for their care attended the Furaha Teens program; and • Attended in the Furaha Teens program.

**Table 3 Tab3:** Inclusion for secondary data study participants

Study participant group	Secondary data inclusion criteria
Adolescents (*N =* 50,000)	• Adolescent girl aged 9 to 14; • Participated in the Kizazi Kipya Project; • In the same household as her parent/caregiver at least 4 days a week; • Parent/caregiver attended the Kizazi Kipya Project; • Consent provided by primary caregiver responsible for the adolescent’s well-being; and • Assent provided by the adolescent.

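### For RQ3, the one nesting level named (parenting group) lies below the facilitator, coach and LIP predictors, so their standard errors are too small if outcomes vary by facilitator or coach

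*Protocol article*

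**What the plan says.** The general rule for clustering, in Quantitative analyses, is one sentence: "Where possible, mixed effect models will be utilized to account for nesting within parenting groups".

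Research question 3 plans correlation and regression to see whether "pre-post changes in family outcomes are associated with family attendance, facilitator and coach competent adherence, and facilitator and coach characteristics", and adds LIP characteristics to the list. The outcome is measured on the family. Apart from attendance, the predictors are measured on the facilitator, the coach or the LIP.

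Research question 2 has a different outcome: "Correlation and regression analyses will be used to examine the relationship between facilitator and coach competent adherence", together with their associations with family, staff and organizational characteristics. Here the outcome itself is at staff level.

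Research question 5 is the only place that mentions levels again: "Multi-level models will be used to examine differences in pre- to post-intervention family-level outcomes", and "Variation in the pre-post changes will be examined by participant baseline characteristics, and, if possible, by parenting group and LIP". Facilitator and coach are not mentioned there.

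On numbers, the section PLH-Teens in Tanzania says that "Pact is scaling-up PLH-Teens with 444 trained facilitators and 70 coaches", Study participants gives "anonymized secondary data from approximately 50,000 parent-child dyads", and Collaborators and setting lists five LIPs. The article states no intraclass correlation, significance level, group size or number of groups per facilitator.

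**The concern.** A facilitator's adherence score or background is the same for every group that the facilitator leads, and a coach's is the same for every group under that coach. Suppose families of one facilitator resemble each other beyond what group membership explains. A group intercept alone then cannot absorb that resemblance. The model takes several groups sharing one facilitator as several independent observations of that facilitator's score. Standard errors for staff-level coefficients come out too small and confidence intervals too narrow, most of all for coaches, where 70 independent values are spread over thousands of groups.

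This differs from a detail left open. The article does choose a nesting level, and an analyst who follows the sentence literally would fit an error structure that does not match the RQ3 staff predictors. RQ3 is one of the study's six questions, and its answers are meant to guide how the program is delivered in Tanzania and elsewhere. Falsely identified staff predictors would feed directly into that advice.

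**Working it through.** The article contains no power, alpha or intraclass-correlation figure, so there is nothing of its own to reproduce. The check asks what a group-only model does to a nominal two-sided 5% test (the 5% is itself an assumption).

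**Inputs from the article**
- 50,000 dyads, 444 facilitators, 70 coaches. So 50,000/444 = 113 dyads per facilitator, 50,000/70 = 714 per coach, and 444/70 = 6.34 facilitators per coach.
- Group size is inferred. Session observations gives 150 participants over 5 sessions, i.e. 30 people or 15 dyads each. The caregiver total agrees: 155 in all less 80 in focus groups leaves 75, and 75/5 = 15.
- Secondary quantitative data collection lists 444 coach assessments of facilitators, so about one adherence score per facilitator.

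**Assumptions**
- One facilitator per group. Then 50,000/15 = 3,333 groups, 7.5 per facilitator and 47.6 per coach.
- Variance shares vC (coach), vF (facilitator) and vG (group), with remainder vE = 1 − vC − vF − vG.

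**Formulas.** Let m be dyads per group, g_f and g_c the groups per facilitator and per coach, and s = vC + vF + vG + vE/m the variance of a group mean. The ratio of true to assumed variance is
- facilitator predictor: 1 + (g_f − 1)(vF + vC)/s
- coach predictor: 1 + [(g_f − 1)(vF + vC) + (g_c − g_f)vC]/s

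and type I error = 2[1 − Φ(1.96/√ratio)].

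**Worked case, vC = vF = 0.01, vG = 0.03.** s = 0.05 + 0.95/15 = 0.1133.
- Facilitator predictor: 1 + 6.51 × 0.02/0.1133 = 2.15; √2.15 = 1.47; type I error 18%.
- Coach predictor: 1 + (6.51 × 0.02 + 40.1 × 0.01)/0.1133 = 5.69; √5.69 = 2.38; type I error 41%.

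| vC / vF / vG (assumed) | Facilitator predictor | Coach predictor | Simulation (facilitator / coach) |
|---|---|---|---|
| 0 / 0 / 0.05 | 5% | 5% | 5.5 / 4.9% |
| 0 / 0.005 / 0.045 | 8% | 8% | 8.6 / 8.1% |
| 0.005 / 0.005 / 0.04 | 12% | 28% | 12.7 / 28.6% |
| 0.01 / 0.01 / 0.03 | 18% | 41% | 17.5 / 43.1% |
| 0.02 / 0.03 / 0.05 | 26% | 49% | 27.3 / 49.1% |

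The simulation used 3,000 runs per row, with 444 facilitators, 70 coaches and 3,330 groups of 15.

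**Sensitivity.** With groups of 10 to 20 dyads, and either one facilitator or a fixed pair per group (a pair doubles the groups per staff unit, while groups per coach stay at total groups/70), the rows with staff-level variance span about 8–45% for a facilitator predictor and 8–57% for a coach predictor.

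**Does the remedy work?** In the same simulation, analysis at the predictor's own level gave 4.7–5.5% for facilitator predictors and 4.7–6.0% for coach predictors. Allowing for facilitator but not coach still left 18–24% for a coach predictor when the coach share was 0.005 to 0.02, so both levels are needed.

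**RQ2, separately.** With one score per facilitator and 6.34 facilitators per coach, the variance ratio for a coach-level predictor is 1 + 5.34 × ICC. At an assumed coach ICC of 0.05, 0.1, 0.2 and 0.3 this gives 1.27, 1.53, 2.07 and 2.60, i.e. type I error of 8%, 11%, 17% and 22%. A facilitator-level predictor unrelated to coach stays near 5%.

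**The case against.** The strongest reply is that the sentence names parenting groups without saying that they are the sole level. Research question 5 speaks of multi-level models and mentions LIP, Implementation process measures plans identifiers that link staff data to families, and a condensed article may leave the exact random effects to an analysis plan not shown. This stands in part: a reader might infer that the plan rules out facilitator and coach effects, and the text does not say so. What remains is that the one level written down is the wrong one for the RQ3 staff predictors, and no passage supplies the missing levels.

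A reader might also infer that false-positive rates will be several times 5%. The article does not support that as a fact. It gives no variance shares, and with none at staff level the rate is 5%.

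Nor does the parenting-group argument carry over to RQ2. Its outcome is staff adherence, so families in groups are not being counted as replicates. The RQ2 issue is narrower: facilitators share a coach, who also rates them.

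Finally, the error structure must not absorb what the study wants to estimate. Fixed effects for the five LIPs would remove the LIP characteristics that RQ2 and RQ3 set out to examine.

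**Conclusion.** The point holds for RQ3. The stated nesting level lies below the facilitator, coach and LIP predictors, and a model built on it alone understates their standard errors whenever outcomes vary by facilitator or coach. The size is a conditional range: 5% with no such variance, about 8% when it is small, and roughly 25–50% when it is moderate, with coach predictors hit hardest. This rests on assumed variance shares, an inferred 15 dyads per group, one facilitator per group, one adherence score per facilitator, and predictors unrelated to the residual staff effects. Attendance and other family-level predictors are outside the argument. With only five LIPs, inference on LIP characteristics is not supportable under any error structure. For RQ2 the concern reduces to coach-level predictors, at about 8–22% for a coach ICC of 0.05 to 0.3.

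**What to change.** In Quantitative analyses, state that RQ3 models of family outcomes include random intercepts for parenting group, facilitator (or facilitator pair) and coach, crossed where nesting is not strict. Alternatively, use cluster-robust errors at the level of the predictor being tested. Coach-level coefficients should use small-sample degrees of freedom (for example Satterthwaite or Kenward-Roger), since there are 70 coaches.

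Do not put LIP fixed effects into models that estimate LIP characteristics; report comparisons across the five LIPs as descriptive.

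For RQ2, where the facilitator is the unit, add only a coach random intercept or coach-clustered errors. Group-within-facilitator intercepts cannot be identified there with one score per facilitator.

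The change is to model specification only. The identifiers needed to link families to implementation data are already planned under Implementation process measures. The price is wider intervals for facilitator- and coach-level effects.
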